### Sample size and power analysis

This study was primarily powered on detecting a between-comparator difference in the primary outcome (i.e., SCARED score) using ITT analysis. We expect the mean cluster size across the 100 schools to be 2 participants, ranging 2–5. Based on the FYF-SB RCT [28], estimates of ICC ranging from 0.001–0.15 were conservatively used in this power analysis. Our study will have 80% power at 5% significance level, with 100 participants per arm to detect a medium effect size (0.45 of Cohen’s D). Additionally, studies with autistic youth that each compared two active treatments further supported our anticipated effect size and power. Two studies reported significant treatment effects when comparing CBT adapted for autistic youth to other interventions (Standard CBT; Enhanced Standard Community Treatment) [57, 58]. The effect size when comparing these two active comparators was medium in size (ranging from 0.50- 0.63) [57, 58]. The effect sizes from these two studies are nearly equivalent to the effect size used for our current study, given that all are within the medium category according to effect size interpretation [59]. We will also have sufficient power to detect the medium effect size for the secondary outcomes.

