### Procedures

School administrators from each partnering school district will first identify elementary and middle schools in their districts that serve a high proportion of historically underserved youth (e.g., racial/ethnic minority youth; high rates of free and reduced lunch). If they are unable to recruit enough participants from those schools, then district leaders will turn to other schools within their district for recruitment. Two-hundred autistic students from up to one hundred (100) schools across Colorado and North Carolina will be randomized to either ZOR or FYF-SB over the course of the project, with up to 50 schools randomized during one academic year and another 50 schools randomized over a second academic year. Once schools are randomized to condition, a minimum of two ISPs at each school will be consented and participate*.* All ISPs will receive training on how to recognize anxiety and emotion dysregulation in autistic students followed by training in either FYF-SB or ZOR.

After training, ISPs will nominate students in their school that they suspect may meet the study inclusion criteria to form groups of 2–5 students with autism and co-occurring anxiety. Once the screening and qualification processes have been completed, and informed consent/assent has been obtained by trained research staff, pre-intervention measures will be completed. Caregiver- and teacher-report measures may be completed electronically via REDCap while student self-report measures will be completed in person by a member of the research team. If students meet inclusion criteria, they will be given the option to assent into the study. Assent will be obtained at their school and by trained research staff. If they assent, participating students will receive either ZOR or FYF-SB depending on which condition their school was randomized to. FYF-SB and ZOR will be delivered over 12 weeks for a duration of approximately 40 min for each lesson. Post-intervention measurements will be completed within 4 weeks of program completion. Semi-structured exit interviews will be conducted with a purposive sample of students, caregivers, and ISPs to obtain information regarding acceptability, appropriateness, and feasibility of either ZOR or FYF-SB, along with any potential harms. Selected outcome measures will be completed at 6 months follow-up.

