### Analytic plan

Between-arm imbalance of baseline characteristics will be examined using* t* and chi-square tests and evaluated based on summary statistics. Intervention effect of FYF-SB as compared to ZOR will be assessed using Linear mixed effect model (LMM) for continuous outcomes and non-linear mixed effect model (NLMM) for categorical outcome such as school attendance. To account for the design effect of clustering trials, random school (cluster) effect will be in the models for outcome without repeated measures while appropriate covariance structure of LMM/NLMM accounting for both the design effect and the correlation of repeated measures will be used for outcome with repeated measures. Transformation of outcome (i.e., Square root or log) will be used if normality assumption is violated. Any imbalanced potential confounding variables will be adjusted for modeling. Primary analysis will be conducted on intent-to-treat basis (ITT). LMM and NLMM will be the primary method for dealing with missing values without data imputation since missing patterns would most likely be of the missing at random (MAR) pattern. The change score from baseline to the end of intervention is considered to the primary effectiveness endpoint. No type I error adjustment for multiple tests in a single model or multiple outcomes will be applied. *P* < 0.05 is deemed statistically significant. No interim analysis will be performed. To examine the robustness of primary analyses, sensitivity analyses will be conducted, including the same analyses among completers and analyses after missing data are imputed using Markov chain Monte Carlo method.

#### Aim 1

The SCARED and PRAS-ASD are the co-primary outcome variables. Both primary and secondary outcomes will be analyzed using the above discussed LMM/NLMM model with fixed effects consisting of time (i.e., baseline/end of treatment/6 months follow-up), comparator (FYF-SB or ZOR) and their interaction. Intervention effect of FYF-SB as compared to ZOR will be estimated by between-comparator difference in the change score of outcome measure from baseline (i.e., interaction) with 95% confidence interval and be tested statistically under the statistical model.

#### Aim 2

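### Mean cluster size 2, range 2–5, 100 schools and 200 students cannot all hold; at the upper planning ICC of 0.15, 80% power needs a mean group size of at most about 2.7 to 2.9

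*Protocol article*

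**What the plan says.** Under Sample size and power analysis, the protocol article states: "We expect the mean cluster size across the 100 schools to be 2 participants, ranging 2–5". It takes ICCs from 0.001 to 0.15 from the earlier randomized trial of FYF-SB, calls their use conservative, and concludes: "Our study will have 80% power at 5% significance level, with 100 participants per arm to detect a medium effect size", with d = 0.45.

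Under Procedures, the providers at each school are to "form groups of 2–5 students with autism and co-occurring anxiety". The same section sets 200 students and up to 100 schools. There 100 is a ceiling; in the power section it is the working number.

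**The concern.** In a cluster trial with a fixed number of participants, power depends on how many clusters they come from. Fewer, larger groups raise the design effect and lower the degrees of freedom. The power section pairs the smallest group size in its own range with the largest permitted number of schools, and also says that sizes will range up to 5. If groups above 2 are formed and enrolment stops at 200, the trial will have fewer schools than the calculation assumes. The question is how far the 80% claim survives that.

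**Working it through.** **Consistency.** Let every school have at least 2 students. A mean of 2 over 100 schools gives 200 students only if each school has exactly 2. One school with 3 makes 201. Holding the total at 200, groups of 2 to 5 correspond to between 200/5 = 40 and 200/2 = 100 schools. Reading the mean as rounded (say 2.4) reconciles it with the range, but implies 200/2.4 ≈ 83 schools, not 100.

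**Inputs.** From the power section: d = 0.45, 100 per arm, significance level 5%, ICC 0.001 to 0.15. From Analytic plan: "No type I error adjustment for multiple tests in a single model or multiple outcomes will be applied", so each outcome is tested at the full 5%. My assumptions: two-sided test, no loss to follow-up, total fixed at 200, d on the analysed scale.

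**Formulas.** Design effect DE = 1 + (m − 1) × ICC for equal groups of size m. Effective n per arm = 100/DE. Noncentrality = 0.45 × √(effective n / 2). Power comes from the normal approximation, or from a noncentral t with (200/m) − 2 degrees of freedom.

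**The plan's own inputs, m = 2.**
- ICC 0.15: DE = 1.15; effective n = 86.96; noncentrality = 0.45 × √43.48 = 2.967; power = Φ(2.967 − 1.960) = 84.3% (t: 83.6%).
- ICC 0.001: DE = 1.001; power 88.9% (t: 88.3%).

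The stated 80% is therefore not reproduced; it is exceeded by about 4 to 9 points.

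**Larger groups, 200 students, ICC 0.15.**

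| Mean group size | Schools | DE | Power, t | Power, normal | Detectable d at 80% (t / normal) |
|---|---|---|---|---|---|
| 2 | 100 | 1.15 | 83.6% | 84.3% | 0.43 / 0.42 |
| 2.5 | 80 | 1.225 | 81.0% | 82.0% | 0.44 / 0.44 |
| 3 | 67 | 1.30 | 78.5% | 79.7% | 0.46 / 0.45 |
| 3.5 | 57 | 1.375 | 76.0% | 77.4% | 0.47 / 0.46 |
| 5 | 40 | 1.60 | 68.9% | 71.1% | 0.51 / 0.50 |

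**Unequal sizes.** DE = 1 + ((1 + CV²) × m − 1) × ICC. Sizes spread evenly over 2, 3, 4 and 5 have mean 3.5 and CV 0.32. DE is then 1.43 and power at ICC 0.15 is 74.4% (t) or 75.9% (normal).

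**Break-even.** For 80% power (normal), the effective n needed is 2 × ((1.960 + 0.8416)/0.45)² = 77.52, so DE may not exceed 100/77.52 = 1.290.
- ICC 0.15: m = 1 + 0.290/0.15 = 2.93 (t: about 2.7).
- ICC 0.10: m = 1 + 0.290/0.10 = 3.9 (t: about 3.5).
- ICC 0.05: m = 1 + 0.290/0.05 = 6.8, beyond the range. The lowest power for means from 2 to 5 is 82.8% (t: 80.8%), at a mean of 5.

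These limits are for equal groups. Variation lowers them: with CV 0.346, the normal limit at ICC 0.15 becomes 2.93/(1 + 0.346²) = 2.93/1.12 ≈ 2.6.

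**The case against.** The case for leaving the claim alone has real weight:

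- The only expected mean in the article is 2. Up to 200 providers with at least two per school also fits about 100 schools. The 2–5 range can be read as what is permitted, not as a forecast of its midpoint, and no passage predicts a mean of 3 or 3.5.
- The plan claims less power than its inputs deliver, so there is margin. A skewed mix such as 56 schools with 2 students, 12 with 3, 8 with 4 and 4 with 5 (80 schools, 200 students, mean 2.5) still gives about 80.6% at ICC 0.15 (normal, DE = 1.27).
- The power section uses a range of ICCs, and the shortfall appears only towards its upper end.

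All of this stands and limits the size of the point. It does not remove the contradiction among mean, range, schools and total.

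Stronger readings are tempting. A reader might infer that 80% power holds only if every school contributes the minimum. At ICC 0.15 without loss, it survives up to a mean of about 2.7 to 2.9. A reader might also infer that the trial is underpowered. The documents do not show this, because they fix neither a single ICC nor a mean above 2. If 100 schools were kept and groups grew, enrolment and power would rise (300 students at a mean of 3: 92.8%). Finally, the lack of a stated attrition allowance is not a fault here, since an article commonly leaves that to the full protocol or analysis plan.

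**Conclusion.** The planning figures are inconsistent as written: a mean of 2, a range of 2–5, 100 schools and 100 participants per arm cannot all be true. The consequence for power is modest and conditional. At the upper ICC of 0.15, with 200 students and no loss, the 80% claim holds up to a mean of about 2.7 (t) to 2.9 (normal) for equal groups. Beyond that, the shortfall is 0.3 to 1.5 points at a mean of 3, 2.6 to 5.6 points at 3.5 (depending on method and spread of sizes), and 9 to 11 points if every group has 5. At ICC 0.10, power drops below 80% from a mean of about 3.5 to 4. At ICC 0.05 or less it does not drop below 80% for any mean from 2 to 5. These results rest on the assumptions listed with the inputs. The means above 2 are illustrations of the permitted range, not predictions.

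**What to change.** Rewrite the cluster-size sentence and the power statement so that they describe one attainable configuration:

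1. An expected mean group size and its spread.
2. The implied number of schools, 200 divided by that mean, worded as up to 100 to match Procedures.
3. The power for d = 0.45, or the detectable d at 80% power, at ICC 0.15, with the cluster-size variation term included and one method used throughout.

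Alternatively, keep the 80% claim and state its condition: at ICC 0.15 it requires a mean group size of no more than about 2.7, and somewhat less if sizes vary. Any loss to follow-up should appear only as a labelled sensitivity assumption, because the article gives no rate.

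The cost is a few sentences and possibly a slightly less favourable stated figure. No participants, tests or estimates change. Recruitment spans two academic years, so the restated figures could still inform the balance between adding schools and filling groups.

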### Trial status

All universities and, when possible, school district Institutional Review Boards have approved the study procedures. This trial is also registered with clinicaltrials.gov (NCT05863520; May 18, 2023). At the time of submission of this manuscript (Fall 2023), we have enrolled participants (e.g., interdisciplinary school providers, autistic students) from elementary and middle schools for data collection.

## Discussion

Anxiety is common amongst autistic youth [60] and can significantly limit their full participation across home, community, and school settings [61]. In school, anxiety may negatively impact students’ attendance, school performance, peer relationships, and extracurricular participation [4]. Although CBT is the gold standard treatment for anxiety in autistic youth, accessing evidence-based mental health care in community settings is difficult for autistic youth and their families [6, 7]. Schools may be an ideal location to address this gap and to equitably manage the mental health symptoms of autistic youth, yet evidence-based practices such as CBT have not been consistently available in schools. Further, previous work with school administrators, providers, and caregivers has clearly indicated that these partners recognize the significant anxiety that many autistic students experience, yet do not have evidence regarding which CBT programs may be most beneficial to implement within school settings to serve autistic youth more equitably and that address outcomes that are meaningful to autistic students and their families [4, 26].

This trial will address this gap by comparing the effectiveness and implementation outcomes of two CBT programs for autistic students across elementary and middle schools. The two interventions that are the focus of this trial*,* FYF-SB and ZOR, are rooted in CBT principles but manage anxiety in different ways. FYF-SB incorporates psychoeducation and graded exposure (facing fears a little at a time) to specifically target anxiety symptom reduction. On the other hand, ZOR targets emotion dysregulation which often underlies anxiety symptoms, and uses predominantly psychoeducation to teach students strategies to regulate different emotional states. The current trial will also address important implementation questions by also comparing the feasibility, acceptability, and appropriateness of each intervention according to students, caregivers, and school providers, and by examining factors that support and hinder the implementation of each program within school settings.

The development and implementation of this trial was directly informed by autistic students and adults, caregivers, school providers, and administrators. Continued partnership with two advisory boards throughout the trial will help ensure the meaningful engagement of autistic and school partners, the measurement of patient-centered outcomes, and the dissemination of practical information about the strengths and weaknesses of FYF-SB and ZOR so that school leaders and other stakeholders can make informed decisions about program selection to support autistic students.

### Limitations

This is one of the first studies to directly compare the effectiveness and implementation outcomes of two school-based CBT programs for autistic students with anxiety. The cluster randomized trial is designed to use methods that are both rigorous (e.g., the use of masked evaluators for primary outcomes) yet that are also pragmatic within school settings. For example, rather than confirming autism diagnoses using resource-intensive, standardized assessments, this study will include students with an educational identification of autism or who have significantly elevated social communication differences as indicated by one or more screening tools. Thus, it is possible that students will be included who are not autistic. However, this more pragmatic inclusion criteria reduces measurement burden on students and caregivers and likely ensures a sample of students that is more reflective of students with social communication differences being services in schools. In addition to the use of pragmatic measures, this study intends to ensure that ZOR and FYF-SB training procedures are similar in length and format. However, it is possible that that attempting to standardize training and consultation masks meaningful differences in how these two programs are implemented in schools, and/or that some of the continued differences methods may impact how the two programs are implemented. Thus, there will be careful documentation of training procedures and the use of mixed methods to understand the role of training content and format on the ease of implementing the two programs.

## Data Availability

The application described in this manuscript is freely available. Please contact the senior author (JR) for more information.

## Abbreviations

ADOS-2: Autism Diagnostic Observation Schedule
CBT: Cognitive Behavioral Therapy
EDI: Emotion Dysregulation Inventory
EBP: Evidence-Based practice
EBPAS: Evidence-Based Practices Attitudes Scale
FYF-SB: Facing Your Fears, School-Based
ICC: Intraclass Correlation
ICS: Implementation Climate Scale
ILS: Implementation Leadership Scale
ISP: Interdisciplinary School Provider
ITT: Intent to Treat
LMM: Linear mixed effect model
MAR: Missing at random
NLMM: Non-linear mixed effect model
PARS-ASD: Pediatric Anxiety Rating Scale—Autism Spectrum Disorder
SAB: Stakeholder Advisory Board
SAS-TR: School Anxiety Scale – Teacher Report
SCARED: Screen for Child Anxiety and Related Disorders
SCQ: Social Communication Questionnaire
SRS-2: Social Responsiveness Scale, Second Edition
ZOR: Zones of Regulation
